## Abstract

**Background:**

The rapid advancement of IT and the complexity of health care demand innovative nursing education that moves beyond lectures and workshops. Nursing students must acquire clinical knowledge alongside emotional intelligence (EI), empathic communication, and crisis management to respond to patients at risk for suicide. In Taiwan, suicide is the second leading cause of death among university students, underscoring the urgency of suicide prevention training. Generative artificial intelligence (AI) platforms such as AI virtual humans provide immersive, scenario-based simulations that can integrate game-based learning into psychiatric nursing curricula.

**Objective:**

This study evaluates the effectiveness of combining game-based pedagogy with AI virtual human simulations in enhancing nursing students’ EI, empathic communication, and psychological crisis management. Specifically, it aims to (1) foster self-awareness and emotion regulation, (2) strengthen crisis assessment and coping strategies, (3) increase motivation and engagement, and (4) establish an evidence-based framework for nursing education innovation.

**Methods:**

An action research design will be conducted over 2 instructional cycles (36 weeks) within a psychiatric nursing course at a Taiwanese university. Participants are third-year postbaccalaureate nursing students recruited through convenience sampling. In phase 1, five simulation scenarios involving suicide risk presentations—major depressive disorder, bipolar disorder, schizophrenia, substance use disorder, and borderline personality disorder—were developed and validated by experts. Phase 2 applies 2 action research cycles (week 1 to 18 and week 19 to 36) with a single-group pretest-posttest design. Quantitative data include the Adult Emotional Intelligence Scale, administered at baseline and after the intervention. Qualitative data consist of reflection journals and classroom observations. Analysis employs descriptive statistics, paired sample 2-tailed *t* tests or Wilcoxon signed-rank tests, effect sizes, linear mixed-effects models, and thematic analysis.

**Results:**

Scenario development and expert review were completed in phase 1. Cycle 1 (weeks 1-18) has begun from September 2025, with 37 students enrolled, exceeding the sample size target of 32. Postintervention Adult Emotional Intelligence Scale results will be collected by week 16, followed by cycle 2 with a new cohort. Final integration and analysis will occur after week 36 to evaluate intervention effectiveness.

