#### Cycle 2: Sampling and Recruitment

This cycle will be conducted during the second semester (spring term) of the third year for a new cohort of nursing students. On the basis of the results, feedback, and reflective evaluations gathered from faculty and students during the first cycle, the instructional content and design of the GBL activities and AI virtual human interactions will be refined. The revised intervention will then be implemented as part of a second action research cycle, with the aim of enhancing the overall effectiveness of the innovative teaching approach and achieving the study’s educational objectives.

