### Sample Size and Power Analysis

Using G*Power 3.1 (Heinrich Heine University) for a paired sample 2-tailed *t* test (“Means: difference between two dependent means, matched pairs”), we set α=.05, desired power=.80, and a medium anticipated effect size of Cohen *d*=0.50—consistent with meta-analytic estimates for short educational interventions targeting EI. The calculation yielded a required completer sample of 32 students to detect the pretest-posttest difference with 80% power. Allowing for typical nursing-course attrition of 15% to 20%, we plan to recruit 40 participants per cycle, ensuring that at least 32 remain for posttest analysis.

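### The abstract sets 37 enrolled students against a target of 32, but 32 is the number of completers required; the recruitment target is 40, so cycle 1 is 3 short

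*Protocol article*

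**What the plan says.** The Results paragraph of the abstract says that cycle 1 has begun "with 37 students enrolled, exceeding the sample size target of 32". It does not mention any other target, and posttest scores are still to be collected.

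The section Sample Size and Power Analysis gives three separate quantities:

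- **The requirement after attrition.** "The calculation yielded a required completer sample of 32 students to detect the pretest-posttest difference with 80% power". The calculation is "for a paired sample 2-tailed *t* test", with these settings: "we set α=.05, desired power=.80, and a medium anticipated effect size of Cohen *d*=0.50".
- **The attrition allowance.** 15% to 20%, described as typical for a nursing course.
- **The recruitment target before attrition.** "we plan to recruit 40 participants per cycle, ensuring that at least 32 remain for posttest analysis".

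The section Cycle 2: Sampling and Recruitment places the second cycle in the "second semester (spring term) of the third year for a new cohort of nursing students". Cycle 2 students therefore do not add to the cycle 1 sample.

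**The concern.** The figure of 32 applies to students who have completed the posttest. At enrolment, the matching figure is 40. By setting 37 enrolled against 32, the abstract turns a recruitment shortfall of 3 into an apparent surplus of 5.

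What is at stake is the accuracy of a sample size statement in the most-read part of the article. A reader of the abstract alone would conclude that cycle 1 has a margin over its planned size. On the protocol's own attrition allowance it has none, and it would be expected to finish slightly below 32 completers.

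**Working it through.** **Inputs.** All come from Sample Size and Power Analysis except the enrolment count, which is in the abstract: paired t test, two-sided α=0.05, power 0.80, d=0.50, 32 completers, attrition 15% to 20%, 40 recruited per cycle, 37 enrolled in cycle 1.

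**1. Reproducing the plan's figures.**

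- Normal approximation: n = ((z₀.₉₇₅ + z₀.₈₀)/d)² = ((1.960 + 0.842)/0.50)² ≈ 31.4, rounded up to 32. This matches the stated requirement.
- Exact noncentral t (df = n − 1, noncentrality d√n): power is 0.7823 at n=32, 0.7954 at n=33 and 0.8078 at n=34. The exact requirement for 80% is therefore 34, and 32 completers give 78.2%.
- Recruitment, n/(1 − attrition): 32/0.85 = 37.6, so 38; 32/0.80 = 40. The target of 40 reproduces at the upper end of the attrition range.

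**2. The like-for-like comparison.** Enrolled against planned enrolment: 37 − 40 = −3, or 7.5% below target. The abstract's comparison: 37 − 32 = +5. The 37 enrolled also fall one short of the 38 needed at 15% attrition.

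**3. Expected completers from 37.**

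- At 15% attrition: 37 × 0.85 = 31.45, or 31 whole students.
- At 20% attrition: 37 × 0.80 = 29.6, or 29 to 30.
- Largest attrition that still leaves 32: 1 − 32/37 = 13.5%, that is, up to 5 students lost.

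**4. Exact power for d=0.50, two-sided α=0.05.**

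| Completers | Power | Points below the planned 32 |
|---|---|---|
| 29 | 0.7387 | 4.4 |
| 30 | 0.7540 | 2.8 |
| 31 | 0.7685 | 1.4 |
| 32 (planned) | 0.7823 | 0 |
| 34 | 0.8078 | – |

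The last column uses 32 completers as the baseline because that is the number the protocol requires. At equal attrition, 40 enrolled would have given 40 × 0.85 = 34 completers (80.8%) or 40 × 0.80 = 32 (78.2%). The missing three students therefore cost about 3 to 4 points: 80.8 − 76.9 = 3.9 at 15%, and 78.2 − 75.4 = 2.8 or 78.2 − 73.9 = 4.3 at 20%.

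**5. Chance of reaching 32 completers.** This assumes that students drop out independently, which the protocol does not state. With 37 enrolled, the binomial probability of at least 32 completers is 0.51 at 15% attrition and 0.22 at 20%. With 40 enrolled it is 0.86 and 0.59.

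**The case against.** The strongest reply is that this is one clause in an abstract. The sample size section keeps completers, attrition and recruitment apart, so a careful reader can resolve the mismatch. That is true, and it limits the weight of the point. It does not make the clause correct, and a reader of the abstract alone cannot resolve it.

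Second, a reader might infer that under-recruitment is what takes cycle 1 below 80% power. The documents do not support this in full. By the exact method the planned 32 completers already give 78.2%, so full recruitment with 20% attrition would also have been below 80%. Only part of the gap belongs to the missing students.

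Third, a reader might infer that cycle 1 will fall short of 32 completers. The 15% to 20% is a planning allowance, and no cycle 1 attrition is reported. The shortfall in completers is conditional; the shortfall in enrolment is not.

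Fourth, a reader might infer that a non-significant cycle 1 result would be misread and would steer the cycle 2 revision. Nothing ties that revision to statistical significance. The cycle 2 section bases it on results, feedback and reflective evaluations, and the main Results section on cycle 1 results and expert feedback.

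Finally, the Data Collection and Analysis Plan calls the paired tests ancillary, keeps incomplete cases in a mixed model, and imputes missing posttests. The paired test is therefore not the only basis for conclusions. This does not remove the mismatch: the sample size is stated for completers of a paired t test in each cycle, and imputation does not replace posttests that were never observed.

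**Conclusion.** The point holds as a misreported sample size comparison with a modest consequence. That 37 enrolled is 3 below the recruitment target of 40 does not depend on any assumption.

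The effect on power does depend on assumptions: attrition in the protocol's own range, d=0.50 for the paired differences, and the exact noncentral t calculation. Under these, cycle 1 ends about half a student short of 32 at 15% attrition and two to three short at 20%, with power of about 77% down to about 74% against 78.2% at 32 completers. If attrition is 13.5% or less, the planned number of completers is met. The design and the planned analyses are unaffected.

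**What to change.** In the abstract, replace the comparison with: *37 enrolled of 40 planned (32 completers required)*.

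In Sample Size and Power Analysis, add that at 15% to 20% attrition about 29 to 31 of the 37 are expected to complete cycle 1, giving exact paired-t power of about 74% to 77% for d=0.50. Note in the same place that 32 completers give about 78% power and that 34 are needed for 80% by the exact calculation.

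The cost is text only, with a slightly less favourable power figure on record. No further enrolment and no change to the analysis is needed. The effect sizes with 95% CIs that the protocol already plans can carry the interpretation of cycle 1. Softening the claim that recruiting 40 guarantees 32 completers would be an optional refinement: 40 × 0.80 = 32 is correct as an expected value but leaves no margin at 20% attrition.

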**Conclusions:**

Integrating game-based learning with AI virtual human simulations introduces an innovative, technology-enhanced model for psychiatric nursing education. Anticipated outcomes include improved EI, enhanced empathic communication, and stronger crisis management abilities. Through iterative refinement across 2 cycles, this study will provide empirical evidence on the role of generative AI in nursing education, informing curriculum innovation and supporting AI-driven simulation as a sustainable strategy for competency-based training.

**International Registered Report Identifier (IRRID):**

PRR1-10.2196/80290

## Introduction

### Background

From the perspective of nursing education, the rapid advancement of IT and the continuous evolution of medical knowledge have significantly impacted health care delivery models and the demand for clinical competencies. Modern nurses are expected not only to possess fundamental clinical skills but also to demonstrate professional knowledge, problem-solving ability, critical thinking, and effective collaboration within interdisciplinary teams. Traditional teaching approaches such as lectures, demonstrations, seminars, and workshops are increasingly insufficient to meet the needs of student-centered learning models. A recent meta-analysis found that virtual simulation significantly enhanced clinical reasoning skills among nursing students, especially when scenarios were longer than 30 minutes as well as nonimmersive and followed by debriefing [1]. In response, nursing education has gradually shifted toward innovative and diversified teaching strategies, including problem-based learning, clinical reasoning, and scenario-based simulation. These approaches aim to foster self-directed learning, integrate theory into clinical practice, enhance motivation, promote peer discussion, and cultivate lifelong learning skills.

Generative artificial intelligence (AI), including tools such as ChatGPT and virtual assistants, has been introduced into educational contexts to support personalized learning, prepare students for complex clinical situations, and improve engagement. A scoping review [2] categorized AI-based teaching strategies in nursing into simulation-based learning, AI-augmented instruction, and AI-generated content and tools and reported improvements in clinical understanding and student participation. In Taiwan, research on AI literacy among nursing students, such as the integration of ChatGPT and Copilot into academic writing courses, has shown significant gains in AI competence and writing performance [3].

From a public health perspective, suicide remains a critical global issue. According to the World Health Organization [4], more than 700,000 people died by suicide in 2019—more than from HIV, malaria, breast cancer, or war—making it one of the leading causes of death worldwide. World Health Organization data indicate that 1 in every 100 deaths is due to suicide, prompting new global policies to strengthen suicide prevention efforts and improve training for health care professionals.

In Taiwan, suicide rates have risen steadily in recent years, particularly among individuals aged 15 to 24 years. According to the Ministry of Health and Welfare [5], suicide is the second leading cause of death among young people, with university students facing heightened risks related to academic pressure, interpersonal stress, and mental health challenges. A series of student suicides in 2020 drew national attention to the complexity of suicide-related factors such as academic stress, emotional distress, and interpersonal difficulties. These incidents have highlighted the need for improved mental health awareness and support within educational settings, enabling both students and faculty to better recognize psychological distress, regulate emotions, and manage stress effectively.

International studies suggest that short-term suicide prevention education can enhance nursing students’ confidence, skills, and attitudes toward suicide prevention. However, suicide prevention programs in most Taiwanese universities remain limited to optional “gatekeeper” lectures or brief workshops, making it difficult to evaluate their effectiveness or ensure knowledge transfer to clinical practice. Given that frontline nurses frequently encounter patients at risk for suicide—including those outside of psychiatric departments—there is a pressing need to integrate effective suicide assessment training into nursing curricula. This forms the foundation of this teaching research project, which aims to use generative AI to create AI virtual human simulations. These simulations will allow students to apply knowledge learned in the classroom by engaging in virtual assessment conversations with AI virtual patients, thereby enhancing the students’ suicide risk assessment and recognition skills.

Nursing students not only face academic demands but also the psychological pressures of clinical internships, such as managing emotional responses during patient and family interactions or witnessing medical emergencies. These stressors can lead to emotional distress, anxiety, or burnout. Despite growing awareness of these challenges, few interventions have systematically addressed the dual need for emotional intelligence (EI) development and suicide prevention training in Taiwanese nursing education. Therefore, this study proposes an innovative AI-based teaching approach that integrates EI enhancement, empathic communication, and crisis management skills through game-based learning (GBL) and AI virtual human simulations. The specific aim of this study is to evaluate the effectiveness of this integrated model in improving nursing students’ EI, suicide risk assessment, and psychological crisis management skills, thereby addressing a critical gap in current literature.

### EI Among University Students and Its Relevance in Nursing Education

EI has become a significant focus in mental health research among university students in Taiwan, particularly due to its association with reduced psychological distress and enhanced coping abilities. Multiple studies have shown that higher EI is positively correlated with better mental health outcomes, including lower levels of stress and anxiety; for instance, a study of university students in southern Taiwan revealed a positive relationship between EI and interpersonal relationships, with female students scoring higher in EI than their male counterparts [6]. Another study identified EI as a protective factor that helps buffer the negative psychological effects of stress and adverse life events [7]. In addition, EI can be enhanced through education. A study evaluating an emotion regulation course for Taiwanese university students reported significant improvements in EI scores and reductions in psychological distress after the intervention, highlighting the effectiveness of education-based approaches to fostering EI [8].

In the context of nursing education, EI is not only important but also foundational. The development of self-awareness is a key starting point, as it enhances communication, clinical decision-making, and interpersonal competence. Research has demonstrated a positive correlation between self-awareness and communication ability among nursing students, and courses that emphasize self-awareness have been shown to significantly improve these skills [9]. Furthermore, the integration of mindfulness with self-awareness has proven effective in helping nursing students manage emotional challenges such as countertransference, thereby improving emotion regulation and professional behavior [10].

Emotion awareness and EI are particularly critical in psychiatric nursing, where students must respond to patients with emotionally complex needs. A study by Por et al [11] found that higher levels of EI were significantly associated with better stress management, clinical decision-making, and subjective well-being among nursing students. However, more recent research has revealed that while nursing students may perform relatively well in managing social emotions, they often score lower in emotion awareness—indicating a gap that may hinder emotion regulation in clinical settings. As such, it has been recommended that EI training be formally integrated into nursing curricula to strengthen critical thinking and decision-making skills, leading to improved educational and clinical outcomes [12].

### Integration of GBL Into Nursing Education

GBL has emerged as an innovative educational strategy that incorporates game design elements to enhance engagement, enjoyment, and learning outcomes. While nursing education traditionally emphasizes the development of professional skills and critical thinking, conventional instructional methods often fall short in motivating students or sustaining their interest. As a result, a growing body of research has examined the effectiveness of applying GBL within nursing curricula.

Studies have demonstrated that GBL contributes to improved student motivation and academic performance; for instance, a systematic review by Xu et al [13] found that GBL significantly enhanced nursing students’ learning experiences, particularly by increasing motivation and emotional engagement. Similarly, Reed reported that game-based teaching approaches not only improved knowledge retention [14] and test performance but also elicited more positive student feedback and engagement during class.

A randomized controlled trial by Blanié et al [15] compared game-based simulation with traditional teaching for developing clinical reasoning skills among second-year nursing students in France. Participants were randomly assigned to either a group that used interactive game-based case simulations or a group that studied the same material through text-based methods. Both groups were evaluated using the script concordance test immediately after instruction and again 1 month later. While no significant differences were found between the 2 groups in immediate or delayed clinical reasoning performance, the study highlighted higher levels of student satisfaction and learning motivation in the simulation by gaming game-based simulation group. Students reported that the game simulations provided a more engaging, interactive, and contextually meaningful learning experience.

These findings suggest that GBL holds substantial educational potential in nursing education, particularly in enhancing student motivation, satisfaction, and selected clinical competencies. However, successful implementation requires careful consideration of design, technological integration, and contextual factors. Further research is needed to explore the long-term effects of GBL across diverse educational settings and nursing specialties.

### Integration of AI Technology Into Nursing Education

With the rapid advancement of IT, nursing education has increasingly incorporated various forms of digital and mobile learning interventions. These include mobile apps, electronic learning platforms, and immersive technologies such as augmented reality and virtual reality (VR). In recent years, the global rise of AI has further expanded educational possibilities, although AI has been more extensively developed and applied in clinical health care practice than in nursing education. The emergence of generative AI technologies—particularly after the release of ChatGPT in November 2022—has signaled a transformative shift in education. In light of these developments, nursing education must adapt accordingly.

A meta-analysis by Chen et al [16] on mobile learning interventions in nursing education revealed that, compared to traditional lecture-based instruction, mobile learning strategies significantly improved students’ clinical knowledge, nursing skills, and confidence, while also receiving higher satisfaction ratings from students. In a recent quasi-experimental randomized controlled trial involving 166 third-year nursing students, the effectiveness of simulated learning using AI virtual patients was compared to that of standardized patient simulations. Both methods were found to enhance clinical safety awareness, reduce errors, and improve clinical competence and decision-making. However, students in the AI virtual patient group demonstrated significantly better outcomes in anxiety reduction, confidence building, and decision-making performance, with results reaching statistical significance (*P*<.001). These findings suggest that AI-based simulation in nursing education not only supports the acquisition of evidence-based clinical knowledge but also enhances communication, critical thinking, and patient safety skills [17].

Although nursing has long intersected with technology, the development and application of AI have typically been seen as the domain of computer science, software engineering, and robotics. However, educators should no longer rely solely on traditional classroom methods. Instead, they must actively enhance their technological competencies by integrating tools such as ChatGPT to support content creation and instructional design. When combined with clinical expertise, generative AI technologies can lead to the rapid development of innovative, high-quality teaching materials that increase student engagement and learning outcomes.

In this project, faculty members have been granted exclusive authorization to use the Virti AI virtual human scenario design platform, developed by HTC. After receiving training on AI-generated dialogues using ChatGPT, educators can create customized virtual patient simulations in as little as 30 minutes—enhancing efficiency by a factor of 10 to 100. Virti’s integration of natural language processing further enables dynamic, student-led interactions with AI-simulated patients, promoting clinical reasoning, communication, and knowledge retention. This AI-powered educational approach has the potential to transform nurse training by significantly improving humanistic communication skills in patient care settings.

